**Endpoint**

The primary endpoint was rate of harms per 1000 patient bed days as determined by the IHI Global Trigger Tool methodology. This was assessed in all patients ‘not for resuscitation’ in both the DNAR and UFTO period. The rate of harms per 100 patient admissions was also calculated within each patient group.

Since this was not our initial end point, a more stringent criteria of 0.02 will be considered statistically significant.

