**Statistical Analysis**

The primary endpoint was the rate of harms per 1000 patient bed days in those patients ‘not for resuscitation’, calculated separately for the group of patients with a DNACPR order and those receiving UFTO. The rate of harms per 100 patient admissions was also calculated within each patient group. The UFTO and DNACPR groups were compared by calculating the absolute rate difference between the groups with a corresponding 95% confidence interval. A stratified analysis was then performed by calculating the rate differences within each ward group. Patient characteristics were compared between groups using the Fisher’s Exact test for all categorical variables and the Mann-Whitney test for all continuous variables except age, for which an independent samples t-test was used. This was because all continuous variables except age had non-normal distributions.

The frequency distribution of the type of harms, and the severity and preventability of harms was tabulated for each group. The chi-squared test for trend was utilized where possible to statistically compare between the groups. However, in the case of tables with low expected counts, Fisher’s Exact tests were used.

Difference in proportions were calculated to compare the number of harms contributing to patient death and the number of harms preventable at any level between groups, with corresponding 95% confidence intervals calculated using a recommended method (Newcombe’s method) [1]. The same method was used to compare discussion rates, EWS response and mortality between groups.

A Poisson regression model was fitted to the number of harms data to evaluate the effect of group (UFTO/NFR or DNACPR) on number of harms after adjusting for possible confounders. For the first model, only the group variable was included as an explanatory variable in the model; and then ward was also added; and finally, a model was fitted including all covariates of interest: ward, gender, Charlson co-morbidity score, MEWS score and age at admission. For all models, a log-transformed offset term was included for hospital length of stay, to adjust for differences in periods of observation across patients.

As a sensitivity analysis, negative-binomial regression models were also fitted to account for any over-dispersion in the data. As before, a log-transformed offset term was included for hospital length of stay, to adjust for differences in periods of observation across patients.

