**The IHI Global Trigger Tool Methodology**

The IHI Global Trigger Tool (IHI GTT) was developed by the Institute for Healthcare Improvement (IHI) to identify “harm” which has occurred to patients in hospital. A UK version has become widely used since 2009. The GTT has a series of objective “triggers”  - for example a fall, or a lack of early or EWS requiring response.

Primary review will be conducted in accordance with the IHI guidelines in a standardised fashion (outlined in a Standard Operating Procedure in an appendix to this protocol) and in 20 minutes or less, by one of two reviewers. Primary reviewers, one research nurse and one junior physician, will review case notes in a random order. Using predetermined selected modules of the UK Global Trigger Tool, any of the 29 triggers met (not just those which they think might be associated with a harm) will be recorded into a filemaker database. Primary reviewers will write a paragraph or two describing each trigger event, no determination of the presence of harm will be made at this stage. Multiple triggers can be recorded for an individual patient. This first 20 sets of notes will be reviewed by both primary reviewers to establish inter-rater reliability and standardization of the review process.

Secondary Consultant physician reviewers will then review the information prepared by primary reviewers. The secondary reviewers will be blinded to demographics, dates of admission and discharge, ward, and whether the patient was in the DNAR or UFTO group.

To maximise concordance, focus specifically on what occurred during the admission, and to minimise confounding, some additional criteria not included in the standardised GTT were predetermined before rating of harm, again outlined in more detail in the SOP for GTT review in an appendix to this protocol.

Secondary reviewers will independently assess each blinded record, determining the presence of a harm associated with a trigger. Where a harm is present, the severity and preventibility will also be recorded. Severity will be classified using the index of the National Coordinating Council for Medication Error Reporting and Prevention (NCC MERP) This gives five categories of harm- category E: temporary harms requiring intervention; category F: temporary harms

requiring initial or prolonged hospitalization; category G: permanent harms; category H:life- threatening harms; and category I :harms causing or contributing to death.

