***Secondary objectives***

We will assess, along with legal, health economic and ethical implications, whether the form:

Increases care for those documented as not for resuscitation, but for active treatment (defined as active treatment in the UFTO group, and no statement of ceiling of care in the DNACPR group). This will be measured by:

- 1. review by other specialities
  2. referral and acceptance to escalating care (e.g. HDU / ICU)
  3. radiological investigation
  4. prescription of “expensive” drugs (where “expensive” is from a predefined list supplied by pharmacy);

Specifically, we will assess whether introduction of the UFTO alters *in isolation and as a composite endpoint* the above mentioned factors.

- Alters length of stay or in-hospital mortality;
- Improves care towards the end of life by encouraging advance care planning;
- Reduces the number of patients who remain inappropriately for resuscitation as judged by total numbers;
- Improves understanding in all groups about the appropriate implications of the decision not to resuscitate, as assessed by qualitative interviews and questionnaires and ethnographic research;
- Creates a positive framework for discussions of treatment options with patients and their families, as assessed by qualitative interviews and questionnaires and ethnographic research;
- To map the current decision-making processes around resuscitation: both explicit and implicit factors, across all groups
- To assess all groups’ attitudes and feelings about the old DNACPR and new UFTO, and compare their differing perspectives
- To assess the ethical problems faced by professional staff in using the conventional DNACPR form and the new UFTO
- To establish what elements of experience from each differing perspective are felt to be associated with the question of resuscitation in order to recognise the ways it has meaning in terms of the overall expectations of care
- To learn from outcome data of the above to inform an optimised approach to resuscitation decisions framed by the UFTO.

Trial Design

EVALUATION OF THE UFTO

The form to be trialled has been developed as described in the introduction

Study Summary

A before and after study will be carried out on the respiratory and general medicine ward, and General Medical/endocrinology and elderly care ward (G4) at the West Suffolk Hospital. Patients under 18 or for palliative care only on admission or who have an admission of less the 24 hours will be excluded.

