**Data Collection**

Data will be collected from the medical and nursing notes by [name] on

- Patient demographics (baseline observations and MEWS, age, gender, diagnosis, comorbidities, number of medications on admission),
- Dates of admission, and discharge/death to determine length and outcome of stay,
- Dates of initiation of palliative care, when applicable
- Ward
- DNACPR/UFTO completed (date, discussion documented, details on form)
- MEWS scores over 3 documented, with date and score.
- Appropriate (as defined by MEWS Score) and timely (within 4 hours) referral to Outreach services
- Referral to ICU/HDU/Out-of-hours medical escalation / medical speciality referral
- Number and type of radiological investigations
- Expensive drugs used
- Date and place of discharge
- Details of discussions / decisions in notes regarding end of life planning, resuscitation decisions, etc. (staff details will also be anonymised).

Data collected from the notes about number of resuscitation calls, and outcomes from these calls will be correlated with the information collected routinely by the resuscitation officers, to ensure accuracy of data.

The hospital Information team will provide data on patient mortality; we will calculate rate of mortality at 30 days post admission for all patients admitted during the study period.

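### The fullest harm model leaves out number of medications on admission and diagnosis, both collected at baseline, so confounding by drug burden or acute case mix may remain

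*Protocol*

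**What the plan says.** The study is a before-and-after comparison: "A before and after study will be carried out on the respiratory and general medicine ward" and on a second ward (protocol, Study Summary).

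The amendment's Statistical Analysis section compares the harm endpoint first without adjustment: "The UFTO and DNACPR groups were compared by calculating the absolute rate difference between the groups with a corresponding 95% confidence interval". It then fits Poisson models "to evaluate the effect of group (UFTO/NFR or DNACPR) on number of harms after adjusting for possible confounders". The models are nested: group alone, then group and ward, and finally "a model was fitted including all covariates of interest: ward, gender, Charlson co-morbidity score, MEWS score and age at admission". Each has a log length-of-stay offset. Negative-binomial versions are the sensitivity analysis.

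The Data Collection section lists the baseline variables: "Patient demographics (baseline observations and MEWS, age, gender, diagnosis, comorbidities, number of medications on admission". Diagnosis and number of medications appear there, beside variables that the model does use. They appear in no harm model, and the document does not say why.

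**The concern.** In a non-randomised comparison, the adjusted model is where patient-level differences between the periods are meant to be handled. Two features of the protocol make such differences plausible.

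- The windows fall at different times. The Study Summary sets a three-month baseline, then education, then a one-month bedding-in period. The second window therefore opens at least 3 + 1 = 4 months after the first, and one of the wards is respiratory.
- The analysed group is itself open to change. Under Trial Aims, the form is expected to reduce the number of patients who inappropriately remain for resuscitation. If it does, the not-for-resuscitation group in the second period will be selected differently from the group in the first.

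If drug burden or reason for admission shifted between periods and also predicts harm, part of that shift would be credited to the form or would mask its effect. The covariate list is described as complete, so the protocol itself settles the question and does not leave it to a later document.

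**Working it through.** **Step 1. Compare the two lists.**

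| Baseline item (Data Collection) | In the fullest harm model (Statistical Analysis)? |
| --- | --- |
| Baseline observations and MEWS | Yes, as MEWS score |
| Age | Yes |
| Gender | Yes |
| Comorbidities | Yes, as Charlson score |
| Diagnosis | No |
| Number of medications on admission | No |

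Ward is collected separately and is in the model.

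**Step 2. Ask whether the included terms cover the gap.** Charlson summarises chronic disease, MEWS summarises physiology, and ward separates respiratory/general medicine from elderly care/diabetes and endocrinology (Number of Subjects). MEWS and ward carry part of the acute case mix. Both wards are mixed, so ward is only a coarse stand-in for diagnosis. No term measures drug burden directly.

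**Step 3. Illustrate the size.** The protocol gives no figure for imbalance or for effect on harm, so there is no stated figure to reproduce. Every input below is an assumption.

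*Binary factor.* Let the factor multiply the harm rate by R, with prevalence q0 in the DNACPR period and q1 in the UFTO period. A true rate ratio of 1 then appears as

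(1 + q1(R − 1)) / (1 + q0(R − 1)).

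Example: q0 = 0.50, q1 = 0.40, R = 1.5 gives (1 + 0.20)/(1 + 0.25) = 1.20/1.25 = 0.960. With q0 = 0.50 throughout:

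| q1 | R = 1.25 | R = 1.5 | R = 2.0 |
| --- | --- | --- | --- |
| 0.50 | 1.000 | 1.000 | 1.000 |
| 0.45 | 0.989 | 0.980 | 0.967 |
| 0.40 | 0.978 | 0.960 | 0.933 |
| 0.30 | 0.956 | 0.920 | 0.867 |

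*Medication count.* Let the harm rate rise by a factor g per drug, given the other covariates, and let the count be shifted by k drugs between periods. The bias factor is g^k.

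- k = 1: 1.03, 1.05 and 1.08 for g = 1.03, 1.05 and 1.08.
- k = 2: 1.03² = 1.06, 1.05² = 1.10, 1.08² = 1.17.
- k = 0: 1.00 whatever g is.

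The binary table ignores whatever ward, Charlson, MEWS and age already absorb. The residual bias is smaller to the extent that those terms track the omitted factor. The same holds for g^k if g or k is taken without conditioning on them.

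**Step 4. Check whether precision would improve.** In a Poisson log-linear model with an intercept and a group term, the fitted totals in each group equal the observed harm counts, E1 and E0. The information on the group coefficient is the weighted sum of squares of group after regression on the other covariates. It cannot exceed its value with no other covariates, E1·E0/(E1 + E0). The model-based variance is therefore at least 1/E1 + 1/E0, whatever is added. More covariates cannot sharpen the Poisson estimate. A gain is possible only where over-dispersion is modelled, as in the negative-binomial analysis.

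**The case against.** The stated set (demographics, comorbidity, acuity and ward) is coherent, and which further covariates to add is partly judgement. Four stronger readings are tempting, and the protocol does not support them.

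- **That confounding is present.** This needs medication count or diagnosis to differ between periods and to predict harm beyond the listed terms. The protocol shows neither.
- **That the full model is the only protection.** The amendment also has contemporaneous comparison groups (patients for resuscitation on the study wards, and patients not for resuscitation on wards without the form), rate differences within ward groups, comparisons of patient characteristics, and secondary review blinded to group. These are real but partial protections: none adjusts individual patients for the two omitted variables.
- **That the harms are largely drug-related.** A reader might infer this because severity is graded on the index of the "National Coordinating Council for Medication Error Reporting and Prevention". The index is used only to grade severity. The example triggers are a fall and a problem with early-warning response, and the modules used are not listed.
- **That the longer list should become the main model.** The amendment followed an initial analysis of the study data, and its analysis section is written largely in the past tense. Replacing the stated covariates now would invite a charge of choosing the model after the fact.

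It is also fair that the Data Collection section describes the original dataset. Availability for study-ward patients in the harm analysis is a reasonable inference. For the comparison wards it is not stated.

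What remains is that the model's stated purpose is to adjust for confounders, and two baseline variables the study set out to collect are left out without a reason.

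**Conclusion.** The point holds in a limited form. The fullest harm model omits two recorded baseline variables that could plausibly confound a before-and-after comparison of harm, so residual confounding is possible and none of the stated models examines it.

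The size is unknown. The illustrative factors, 0.87 to 0.99 for a binary factor and 1.03 to 1.17 for medication count, rest wholly on assumed effects and assumed imbalances; the direction of the bias depends on the direction of the imbalance. With no imbalance the bias is zero.

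This is a modest gap in the adjusted analysis. It does not affect the main comparison, which is unadjusted, and closing it would not cure the design's larger weakness, change over calendar time.

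**What to change.** In the amendment's Statistical Analysis section, add one further nested model to both the Poisson and the negative-binomial series, for the study-ward patients. It contains the stated full set plus number of medications on admission as one linear term and main admission diagnosis in a few broad groups (for example acute respiratory, other acute medical, other). Use admission values only, so that the terms precede exposure to the form. Report it beside the stated full model, not in its place, and label it as an addition.

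The cost is a sentence of text and about three parameters: one for medication count, plus two for three diagnosis groups. Diagnosis group will overlap in part with ward, and some values may be missing, so give the number of patients in each model. The added model should not be presented as removing calendar-time effects, as changing the unadjusted rate difference, or as improving precision in the Poisson analysis.

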**The IHI Global Trigger Tool Methodology**

The IHI Global Trigger Tool (IHI GTT) was developed by the Institute for Healthcare Improvement (IHI) to identify “harm” which has occurred to patients in hospital. A UK version has become widely used since 2009. The GTT has a series of objective “triggers”  - for example a fall, or a lack of early or EWS requiring response.

Primary review will be conducted in accordance with the IHI guidelines in a standardised fashion (outlined in a Standard Operating Procedure in an appendix to this protocol) and in 20 minutes or less, by one of two reviewers. Primary reviewers, one research nurse and one junior physician, will review case notes in a random order. Using predetermined selected modules of the UK Global Trigger Tool, any of the 29 triggers met (not just those which they think might be associated with a harm) will be recorded into a filemaker database. Primary reviewers will write a paragraph or two describing each trigger event, no determination of the presence of harm will be made at this stage. Multiple triggers can be recorded for an individual patient. This first 20 sets of notes will be reviewed by both primary reviewers to establish inter-rater reliability and standardization of the review process.

Secondary Consultant physician reviewers will then review the information prepared by primary reviewers. The secondary reviewers will be blinded to demographics, dates of admission and discharge, ward, and whether the patient was in the DNAR or UFTO group.

To maximise concordance, focus specifically on what occurred during the admission, and to minimise confounding, some additional criteria not included in the standardised GTT were predetermined before rating of harm, again outlined in more detail in the SOP for GTT review in an appendix to this protocol.

Secondary reviewers will independently assess each blinded record, determining the presence of a harm associated with a trigger. Where a harm is present, the severity and preventibility will also be recorded. Severity will be classified using the index of the National Coordinating Council for Medication Error Reporting and Prevention (NCC MERP) This gives five categories of harm- category E: temporary harms requiring intervention; category F: temporary harms

requiring initial or prolonged hospitalization; category G: permanent harms; category H:life- threatening harms; and category I :harms causing or contributing to death.

A Likert scale with scores ranging from 1 for “definitely not preventable” to 4 for “definitely preventable” will be used to evaluate preventability

Cases in which physician reviewers disagree will be discussed, and consensus reached; where this is not possible, a third opinion will be obtained. Inter-rater reliability on the presence of aharm will be calculated from pre-discussion ratings.

# References

# [2] R Development Core Team (2012). R: A language and environment for statistical computing. R Foundation for Statistical Computing, Vienna, Austria. ISBN 3-900051-07-0, URL <http://www.R-project.org/>.

[3] **SPSS/PASW for Windows, Rel. 18.0.3. 2010. Chicago: SPSS Inc.**

Introduction

Background

Do Not Attempt Resuscitation (DNACPR) orders are likely to affect all people directly or indirectly: 68% of the population dies in hospital(1) and 80% of those die with DNACPR forms in place(2). DNACPR forms do not only affect those who are dying: many patients with DNACPR forms are discharged home(3).

DNACPR forms instruct the clinical team what to do in the event of a cardiac or respiratory arrest, and are not meant to affect other aspects of care(4).

They are filled in when a physician believes that a patient would not benefit from attempted resuscitation, or at a patient’s request. There is no legal obligation to tell a patient that such a form has been completed for them and a patient has no legal right to demand its removal.

In clinical practice we observed multiple problems with the current use of DNACPR forms.

• A reluctance amongst colleagues to refer patients with DNACPR orders for more intensive treatments;

• Hesitation before filling out a DNACPR form on patients, for fear it might have farther reaching impacts;

• Lack of communication between teams clarifying extent of treatment that was appropriate

• Variability in consultant practice for filling out DNACPR forms, resulting in the unethical situation where the decision concerning resuscitation for the individual patient was often made on an ad hoc basis. This can result in patients having resuscitation inappropriately attempted, with resulting discomfort, lack of dignity, and associated health costs

We investigated these further with preliminary studies and literature reviews as detailed below, and have summarised the ethical challenges that these problems pose in a paper in the Journal of Medical Ethics (5).

Patients, carers and health care professionals are uncomfortable discussing DNACPRs(6-8), although studies have also shown that, when asked, patients would like to have these conversations, despite the associated distress(9, 10).

Significant variability exists in the manner that DNACPR is approached and in the frequency of DNACPRs being implemented(11). Local data supports this (annex 4). This variability increases the difficulty of discussing DNACPR.

There is evidence that DNACPRs are misinterpreted to mean that treatments other than resuscitation should be withheld or diminished (12-14). A recent questionnaire carried out in our hospital amongst 50 doctors and 35 nurses confirmed this (15).

Consistent with this studies have shown that DNACPRs alter patient care; Beach et al (16) carried out a survey of doctors on hypothetical patients, and demonstrated that the presence of a DNACPR had an effect on decision making.

Those with DNACPRs have less intensive care (17, 18) and increased mortality (19, 20)

Alternatives to a DNACPR have been created, and their impact on documentation (21, 22), rate of CPR attempts and ventilation (23) assessed.

Advanced care plans have been developed to improve end-of-life care for palliative patients (24), but to our knowledge, a Universal Form for Treatment Options (which would be filled out on every patient, and include multiple treatment options) has never been developed, nor has the impact of any alternative to the DNACPR been assessed for changes in patient care and survival outcomes.

We interviewed 19 senior medical and nursing members of the hospital from all adult specialities (summary of interviews: annex 4) and had a consultative meeting with 2 lay panels (minutes: annex 4) to reach consensus on an alternative to the DNACPR form. We then had meetings with a physician panel, two nurse panels, and a further patients panel. The form was assessed with volunteer doctors and an actress to test out use. The result of this consultative process is the Universal Form for Treatment Options (UFTO) It was then piloted for two weeks, and further assessed with a cohort study at the West Suffolk.

The Investigators

[name] is a Specialist Registrar in Acute Medicine and Intensive Care, and a board member of the Institute for Medical Ethics. Her initial observations, literature search and preliminary studies led to the formulation of the research question. [name] is a consultant in Acute and Respiratory Medicine. He is the local clinical lead for a large quality improvement initiative and has experience managing randomised controlled trials. [name] is a Medical Anthropologist with extensive research experience of patient and professional perspectives. He will manage the qualitative components of the project. [name] is Director of the Centre for Applied Medical Statistics, Cambridge and provides expertise in research design and data analysis. [name] is a Consultant in Respiratory Medicine and Clinical Director for Medicine at West Suffolk Hospital. She has an MD and has previously held two large NHS Executive research grants. [name] holds the chair of Medical Ethics at Oxford; he will lead on the ethical implications of the project. [name] is a Lecturer in Health Economics, and has conducted economic evaluations within a number of pragmatic RCTs. [name] is Assistant Director Medico-Legal and Patient Experience at Cambridge University Hospital Hospitals and brings legal and ethical expertise. [name] is an early career social anthropologist, with research interests in shared decision-making in medicine. [name] is a research nurse with specific expertise caring for the critically ill.

12 lay individuals comprise an advisory group. They come from varied backgrounds; all have had experiences with resuscitation decisions either regarding themselves or a loved one.

Trial Aims and Objectives

Trial Aims:

The aim of this trial is to evaluate the UFTO, as an alternative to DNACPR, in reducing inequities of care resulting from current approaches to resuscitation decisions and documentation.

We hypothesise that use of the UFTO will

- contribute to a standardisation in doctors’ approaches to DNACPR decisions, whilst allowing patients’ individual choices to be respected;
- increase the number of discussions (both patient-initiated and doctor-initiated) which take place between doctors and patients about treatment decisions;
- encourage the documentation of clear treatment plans on what to do in the event of a patient’s sudden deterioration;
- reduce the number of patients who die in hospital without clear guidance as to appropriateness of resuscitation attempts from currently close to 20% to close to 0%. We hypothesise that this will result in fewer patients inappropriately remaining for attempted resuscitation;
- remove inequalities of treatment currently associated with a DNACPR form;
- increase satisfaction with and frequency of discussions pertaining to resuscitation decisions. Such benefits should be demonstrable in all groups;
- serve as the basis for general guidelines around the resuscitation discussion, so that doctors feel more supported when raising the topic with patients and relatives, who in turn experience it as an appropriate and necessary part of their overall care.

We aim to evaluate this using both quantitative and qualitative research methods.

*Primary objective*

To assess whether the UFTO improves the number of timely referrals in response to MEWS (modified early warning system)≥ 3 in those patients who are documented as not for resuscitation.

[*MEWS* is an objective physiological scoring system, based on pulse, blood pressure, etc. (detailed below, under section ‘Quantitative Analysis’)

*Timely* is defined as within 4 hours of the MEWS score being recorded

*Referrals* include referrals to the outreach team and the doctors.]

